## Abstract

**Background:**

Sarcopenia, altered bone and systemic metabolism, physical frailty and cognitive decline are age-dependent and interrelated phenomena. Sleep disorders which are erroneously considered as part of the aging process might be the unifying underlying mechanism of accelerated aging. It is well-known that impaired sleep health could predict neurodegeneration and functional decline. However, in current clinical practice, sleep disorders are not routinely screened and only a minority of cases require second-tier specialist techniques. The delay of their assessment, without a comprehensive evaluation, results in higher healthcare costs. The aim of SOMNUS-DARE project is to detect, in a translational manner, the role of sleep disorders in the genesis of physical frailty, sarcopenia, mild cognitive impairment, and to measure their contribution to the progression of these phenomena towards mobility-disability and dementia.

**Methods:**

SOMNUS-DARE project will evaluate a sample of 300 community-dwelling healthy active and physically frail sarcopenic subjects, aged 65 years or older, free of cognitive impairment and self-sufficient in basic activities of daily living. The effect of sleep disorders on physical, cognitive and cardiovascular function, systemic, bone and muscle metabolism and body composition will be prospectively assessed by performing: comprehensive geriatric assessment; sleep analysis and environmental monitoring; brain MRI, amyloid positron emission tomography; bone densitometry; radiofrequency echographic multi spectrometry; muscle ultrasound; bioimpedance analysis; cardiac ultrasound; dynamic blood pressure monitoring; blood and saliva measurements.

**Discussion:**

The project will make it possible to analyse an extremely relevant public health problem which is still underestimated in the current clinical practice. The combination of traditional diagnostics and innovative digital health techniques, will allow a translational and multidimensional analysis of sleep disorders and to weigh their impact on physical and cognitive decline and quality-of-life trajectories. The expected results will highlight the importance of sleep as a fundamental determinant of health and will contribute to the activation of clinical diagnostic and therapeutic pathways in older individuals where the tailored approach might contribute to substantial benefit.

**Trial registration:**

Clinical Trial Number: NCT06944600; Clinical Trial Registry: ClinicalTrials.gov; Registration Date: April 17th, 2025.

## Background

### The complex interplay between sleep health, brain, muscle, bone, body composition, endocrine and cardiovascular systems

Skeletal muscle health and brain integrity are strictly interconnected, with sleep as a shared regulatory factor for their trajectories. This contribution of sleep profile could be particularly relevant for sarcopenia, physical frailty, and mild cognitive impairment (MCI) in older adults. In this population, sleep disorders—often misattributed to normal aging—can precipitate the progression from these conditions toward mobility- disability and dementia, by disrupting attention, motivation, emotion, decision making, executive functions, motor control, learning and memory consolidation [1]. Micro-architectural sleep features are central to this link and a reduction in the cyclic alternating pattern (CAP), an electrophysiological marker of NREM sleep instability, is an example. Impaired sleep microarchitecture, as expressed by CAP impoverishment, reduces glymphatic clearance during sleep, increasing β-amyloid burden accumulated across the day (Fig. 1). It may function both as an early marker and a driver of neurodegeneration, identifying MCI patients at high risk for dementia and those with alpha-synucleinopathies such as Parkinson’s disease [2–7].

**Fig. 1 Fig1:**
[figure not shown]
Schematic representation of the glymphatic theory

Sleep anomalies—including poor quality, extreme duration (short or long), prolonged latency, sleep-disordered breathing, and daytime sleepiness—associate with frailty [8]. Sarcopenia, a major determinant of physical frailty, is modulated by sleep via anabolic and catabolic hormonal pathways. In particular, protein synthesis, muscle repair, and the release of growth hormone (GH), insulin-like growth factor 1 (IGF-1), testosterone, insulin, and cortisol are sleep-dependent and circadian-modulated, as evidenced by the dysregulation of the hypothalamus–pituitary–adrenal axis (HPA) due to chronic insomnia [9] (Fig. 2).

**Fig. 2 Fig2:**
[figure not shown]
Schematic representation of the restorative theory

Therefore, restoring favorable sleep patterns may physiologically re-activate somatotropic and HPA axis function, supporting muscle recovery and delaying age-related sarcopenia [10]. Observational data suggest a U-shaped relationship between sarcopenia risk and sleep duration: both short and long sleep, relative to normal duration, increase risk in community-dwelling older people [11]. Consistently, short (≤ 5 h/day) and long (≥ 8 h/day) sleepers show lower lean mass and higher fat mass; these sleep characteristics shape body composition and physical performances, being foundational to sarcopenic obesity [12]. This relationship between sleep disorders and sarcopenic obesity is bidirectional [13]. Specifically, EPISONO and ELSA-Brasil cohorts link obstructive sleep apnoea (OSA) and nocturnal hypoxia to sarcopenic obesity [14], while OSA risk is higher in older obese adults with low muscle mass and strength [15]. Hence, coexisting sleep disorders, sarcopenia, and adverse body composition potentiate each other’s consequences, underscoring intervention targets across this intertwined pathophysiology—often initiating in midlife [16].

Cardiovascular diseases (CVD) mediate the sleep–frailty nexus, through bidirectional sleep and cardiac-skeletal muscle interactions [17]. Evidence, including our past research experience [18], demonstrates frequent coexistence of CVD and frailty, with the latter worsening outcomes and recovery of the formers [19]. In older sarcopenic and physically frail adults, appendicular lean mass positively correlates with left ventricular mass, cardiac output [20], and systemic blood pressure—the main determinant of LV mass [21]. This linkage between myocardial structural changes and skeletal muscle status lays the ground for a cardiac–skeletal muscle axis well established in ‘cardio-sarcopenia’ and firstly studied in European older cohorts [22]. Thus, sleep-disordered breathing, insomnia, fragmentation, and deprivation impair autonomic control, increases oxidative stress and inflammation [23], and disrupts endothelial function, elevating risks of CVD (E.g., hypertension, heart failure, coronary disease, arrhythmias), metabolic disorders (I.e., diabetes and obesity), and frailty [24]. Therefore, early, comprehensive, and multidisciplinary detection of compromised sleep health is critical to reduce cardiometabolic burden and to mitigate frailty onset and progression [25]. Together with muscle and adipose tissue, bone is the third component of a triad that is fundamental to the physical performance of older individuals, as well as contributing factor for physical frailty. Observational and interventional studies suggest that short sleep duration and night shift work negatively impact bone metabolism and health through undefined mechanisms, involving sleep and circadian rhythm disruption, which seems to impact bone formation more than bone resorption [26].

### Lifestyle factors and medications affecting sleep health

Regular physical activity and appropriate eating habits, among the others sleep hygiene measures, including daylight exposure, consistent sleep schedules, smoking cessation, and avoidance of alcohol, caffeine, stress, and intense noise, offers low-cost population-level benefits [27].

The effects of exercise on sleep in older adults remain heterogeneous. Aging degrades sleep quality, increasing daytime fatigue, lowering physical activity and wellbeing, and raising risks of mental, cardiovascular, and metabolic illness [28]. Physically active older adults report fewer sleep complaints, improved sleep efficiency, longer duration, and less effort initiating sleep [29]. Moderate–vigorous activity associates with better sleep quality in small studies [30] and physical activity above 150 min/week may complement insomnia management [31]. Medical sleep monitoring instruments could increase the accuracy of both sleep quality assessment and physical activity evaluation, contributing to determine its real impact on sleep health in older adults [32].

Nutrition influences sleep and age-related disease trajectories [33]. Caloric intake, macro- and micronutrients, alkaloids, and alcohol modulate wakefulness and sleep quality [28]. Low protein intake correlates with poor sleep, whereas high protein consumption may impair sleep maintenance [34, 35], as well as tryptophan—a serotonin/melatonin precursor—supports performance and total sleep time in adults consuming tryptophan-rich foods [36, 37]. In addition, the quality of carbohydrates consumed appears to be crucial for a healthy sleep. Fiber content and processing alter glycaemic index and meal timing, affecting sleep via cortisol/GH/glucagon release and inflammatory pathways [38]. Diets high in sweets or irregular meals associate with poor sleep, whereas whole grains, fruits, vegetables, and seafood support healthy sleep [28]. Moreover, correcting B-complex and vitamin D deficiencies may improve sleep rate and quality [39, 40], as well as magnesium may reduce insomnia through NMDA antagonism, GABA agonism, and melatonin regulation [41]. Furthermore, the correlation between diet, gut microbiota, and the gut–brain axis provides such additional mechanisms as immune signalling, vagal modulation, blood–brain barrier and intestinal permeability, circulating microbial metabolites and reactive oxygen species, as well as serotonergic pathways bidirectionally related to sleep [42].

Psychoactive substances and drugs profoundly affect sleep. Caffeine impairs sleep onset/maintenance by prolonging sleep latency and reducing total duration and quality [43, 44]. Tobacco use associates with reduced sleep efficiency, REM suppression, and increased daytime sleepiness [45], through central nicotinic effects on acetylcholine, glutamatergic, dopaminergic, and serotonergic signalling [46]. Alcohol disturbs sleep architecture and duration, as well as circadian timing [47].

Medications may induce daytime sleepiness (antihistamines, anticholinergics, anticonvulsants, opioids) or insomnia (pseudoephedrine, β-agonists, corticosteroids, antidepressants, methylphenidate, selegiline) [48].

Drug-related exacerbation of comorbid conditions (e.g., respiratory decline or OSA with β-blockers, benzodiazepines, opioids; diuretic-induced polyuria; ACE-inhibitor–related cough) further disrupts sleep. Polypharmacy—commonly defined as ≥ 5 concurrent drugs—raises risks of drug-related problems and adverse outcomes in older adults [49]. Drug–drug and drug–disease interactions and prescribing cascades amplify harm to sleep health [50].

Individually or interacting with each other, these mechanisms can have exponentially deleterious effects on sleep health.

The purpose of our work is to achieve a deeper understanding of how sleep and sleep disorders impact on mild cognitive impairment and cognitive frailty, sarcopenia and physical frailty, accelerating the trajectory toward dementia and mobility disability, leveraging advanced diagnostics and digital health techniques. The analysis will be focused on reciprocal relationships and carried out on both healthy active and physically frail sarcopenic elderly people. In particular, our objective is to detect the changes in brain, muscle, hormonal milieu, cardiovascular system, skeletal and body composition, by outlining their different intertwined trajectories in individuals with and without sleep disorders, in a comprehensive and translational framework (Fig. 3).

**Fig. 3 Fig3:**
[figure not shown]
Impact of sleep disorders on ageing trajectories and related pathophysiological implications

## Methods

### Objectives

Detect, in a comprehensive and translational way, changes in brain, muscle, hormonal milieu, cardiovascular system, skeletal and body composition to gain a deeper understanding of the impact of sleep disorders on mild cognitive impairment and cognitive frailty, sarcopenia and physical frailty, dementia and mobility disability.

The primary objective is to evaluate the effect of sleep disorders on the incidence of physical and functional worsening from the baseline to 12 months [51–53].

The secondary and exploratory objectives are listed in Table 1.

**Table 1 Tab1:** List of secondary and exploratory objectives/outcomes

**Secondary objectives/outcomes** *To be evaluated in healthy active and/or physically frail sarcopenic older individuals with and without SD*
Prevalence and incidence of sarcopenia *according to sex specific cut-points recommended by EWGSOP2* [54]
Prevalence of MCI and cognitive frailty
Effect of sleep disorders on the incidence of MCI and cognitive frailty
Effect of sleep disorders on the incidence of dementia in cognitively frail participants
Prevalence and incidence of recognised pre-frailty conditions (I.e., MCR)
Prevalence and incidence of malnutrition, polypharmacy and multimorbidity
**Exploratory objectives/outcomes** *To be evaluated in healthy active and physically frail sarcopenic older individuals with and without SD*
Radiological, ultrasonographic, and bioimpedance changes in bone, muscle, and body composition
Magnetic resonance and nuclear medicine brain changes
Ultrasonographic and functional cardiovascular system changes
Anthropometric parameters and nutritional measures changes
Quality of life, social well-being, and reward level changes
Use of healthcare services changes
Differences in mortality
Criterion validity between MMSE score and brain MRI/Amyloid PET
Criterion validity between neuropsychological assessment and brain MRI/Amyloid PET
Role of recognised pre-frailty conditions (I.e., MCR) in affecting the adherence to a multi-component treatment

*Abbreviations*: *SD* Sleep disorders, *MCI* Mild cognitive impairment, *MCR* Motoric cognitive risk syndrome, *MMSE* Mini mental state examination, *MRI* Magnetic resonance imaging, *PET* Positron emission tomography

### Study design

The SOMNUS-DARE is prospective cohort study improving both the previous SPRINTT project [18] and the current Trajector-AGE (Clinical Trial Number: NCT06168591; Clinical Trial Registry: ClinicalTrials.gov; Registration Date: December 4th, 2023) study [55] expertise. The exposure is represented by the sleep disorders, and the primary outcome is the physical and functional worsening. The duration of the study and the follow up shall be nearly 24 months, according to the time of enrolment in the study and interim power reassessment. Upon approval by the Ethics Committee, the first 6 months will be dedicated to the team members’ training, the participants' enrolment, and the database setup and logistics arrangement. In order to maximize the statistical power of the analyses, each participant will be insured the same follow-up's length, according to the date of his/her recruitment. Those who will be enrolled at the beginning of the recruitment phase will have the same follow-up duration compared with those who will be included at the end of recruitment. Therefore, a 2-year follow-up will be guaranteed. Participants’ follow-up will take place at 3 time points: baseline, 12 and 24 months, by performing the measurements described below in the specific chapter (Fig. 4). The final 6 months of the study will be devoted to progressively carrying out of all the end-of-study visits and measurements, database cleaning and statistical analysis, as well as to predisposing both submission of papers to international scientific journals and disseminating results in international and national conferences.

**Fig. 4 Fig4:**
[figure not shown]
Schematic representation of the SOMNUS-DARE study design

### Setting and participants

Physically frail sarcopenic [3 ≥ Short Physical Performance Battery (SPPB) score ≤ 8] and healthy active [SPPB score > 8] [51] subjects from 65 years of age and afferent the geriatric and sleep medicine outpatient clinics, not demented and independent in the Basic Activities of Daily Living (ADL), will be categorized on the basis of the reduced sleep quality, self-reported and screened by the Pittsburgh Sleep Quality Index [PSQI (Italian version)] [56, 57] and stratified for the usual level of physical activity assessed by Physical Activity Scale for the Elderly [PASE-I (Italian version)] [58, 59]. The following eligibility criteria are intended to select a population that is at risk of accelerated decline in aging trajectory due to sleep disorders and their related systemic consequences. This age-group shall be selected for the sufficient long-life expectancy: to participate in a longitudinal study that lasts up to 2 years. Targeting this subset of the elderly population we will be able to recruit a non-disabled but at-risk population for a research project employing digital and eHealth technologies for frailty and disability assessment and prevention. Furthermore, we are planning to evaluate the eligibility criteria for those subjects previously enrolled in the SPRINTT clinical trial by the Parma site, completed at the end of 2019 and who have not evolved to a condition of disability or dementia, as well as those older individuals screened in the Trajector-AGE study by the same site, started at the end of 2022 and who were found to be sarcopenic and physically frail.

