### Statistical methods

Data will be summarized using mean ± standard deviation (SD) or, for non-normally skewed distributions, as median and interquartile range (IQR). Incidence (mild cognitive impairment and cognitive frailty; dementia; recognised pre-frailty conditions; malnutrition; polypharmacy; multimorbidity), prevalence (mild cognitive impairment and cognitive frailty; recognised pre-frailty conditions; malnutrition; polypharmacy; multimorbidity) and mortality among healthy active and physically frail sarcopenic elderly individuals with and without sleep disorders will be compared using chi-square test, adjusted for age and sex.

According to the sample size estimation, 95% CIs will be calculated with Clopper-Pearson method and tested with a test for two proportions. For interpretative purposes multivariable logistic regression will be implemented. Moreover, to evaluate the outcome in terms of continue variable, multivariable ordinal logistic regression model will be used to estimate the association between the sleep disorders and the single unit of decrease in physical and functional score (SPPB score).

Since there will be multiple measures (baseline, + 12 months, + 24 months), the Mixed Model for Repeated Measure (MMRM) will be adopted for the longitudinal analyses.

The analyses will be centralized and performed by the Clinical and Epidemiological Research Unit at University Hospital of Parma using R-Cran and STATA statistical softwares.

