Our methodological choices, incorporating both subjective and objective measures, as recently recommended by the American Heart Association [128], could comprehensively assess sleep health dimensions and minimize measurement bias. Furthermore, age-adapted analytic procedures we are planning to adopt, could account for interindividual differences and age-related changes in sleep physiology, as highlighted by recent methodological reviews [126].

Anticipated challenges include participant attrition, adherence to sleep monitoring protocols, and potential confounding from comorbidities, psychosocial factors, and medication use. On the other hand, regular follow-up, use of user-friendly wearable devices, robust statistical adjustment for covariates, and optimized sampling frequency represent countermeasures we are planning to involve and which allow to capture sleep variability, and not to miss key biological relationships as well [129, 130].

The project will allow to analyse sleep disorders, a public health problem, in the older population, where it is extremely relevant condition not fully addressed. In particular, reliance on subjective sleep assessment through questionnaires in cognitively frail individuals is known to introduce reporting bias, which can lead to under- or overestimation of sleep disturbances. On the other hand, objective sleep assessment through devices like actigraphs, sleep profilers, and cardio-respiratory monitors can mitigate this bias by providing quantifiable sleep parameters. Therefore, the inclusion of both types of measures, in research and clinical protocols, is known to represent the best opportunity to ensure robust and clinically meaningful assessment of sleep in vulnerable populations, as each provides distinct information: subjective measures reflect perceived sleep quality, while objective measures correlate more closely with sleep architecture. This approach will allow us to assess the sleep misperception, a relevant aspect of sleep health in this population [131–133].

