### Outcomes

The primary outcome is the incidence of physical and functional worsening at 12 months (Fig. 7).

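### The primary comparison is a crude two-proportion test in a non-randomised cohort, so the declared activity strata and the promised covariate adjustment do not reach the primary result

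*Protocol article*

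**What the plan says.** All of this is in the protocol article.

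- Study design describes a prospective cohort: "The exposure is represented by the sleep disorders, and the primary outcome is the physical and functional worsening". Nobody is allocated to the exposure.
- Setting and participants categorises participants by self-reported sleep quality (PSQI) and has them "stratified for the usual level of physical activity assessed by Physical Activity Scale for the Elderly". It gives no cut-points, quotas or reason for the stratification. PASE is part of the comprehensive geriatric assessment.
- Outcomes: "The primary outcome is the incidence of physical and functional worsening at 12 months". The event is SPPB below 9 in healthy active participants and failure of the 400 m walk in physically frail sarcopenic participants.
- Statistical methods links the main comparison to the sample size estimation, which was done for the primary endpoint: "95% CIs will be calculated with Clopper-Pearson method and tested with a test for two proportions". The next sentence reads: "For interpretative purposes multivariable logistic regression will be implemented". Its covariates are not listed.
- The secondary incidence, prevalence and mortality comparisons "will be compared using chi-square test, adjusted for age and sex".
- The Discussion counts the ability to adjust for confounders as a strength and offers "robust statistical adjustment for covariates" as a countermeasure to confounding, among other challenges.

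**The concern.** In a cohort, classifying people by a third factor removes no confounding unless the analysis uses the classes. Here the method for the primary endpoint is stated, and it is crude. The adjusted model has a lesser role, so even a full covariate list elsewhere would not change which result is primary. The secondary comparisons are adjusted for age and sex, while the primary one is adjusted for nothing.

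Activity is a credible confounder on the plan's own account. The Background says "Physically active older adults report fewer sleep complaints, improved sleep efficiency, longer duration, and less effort initiating sleep", and the groups are formed from a self-report sleep questionnaire. That activity also bears on SPPB or the 400 m walk is plausible, but the article does not quantify it. SPPB group matters as well: the plan expects 9% events in one group and 27% in the other.

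At stake is whether the headline risk ratio describes sleep disorders, or partly describes a less active, frailer or older group of people.

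**Working it through.** **Inputs from the article (Sample size).** N = 300; sleep disorders with:without 2:1, so 200 and 100; healthy active:frail 1:1; expected rates without sleep disorders 9% and 27%; risk ratio 1.55; alpha 5% (taken as two-sided).

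**The plan's own rate.** (9% + 27%)/2 = 18%, which matches the stated pooled rate. With sleep disorders: 1.55 × 18% = 27.9%. The simple average holds only if the frailty split is the same in both sleep groups.

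**Bias from activity (inputs assumed).** Let a and b be the low-activity shares with and without sleep disorders, and r the risk ratio for low against higher activity. If sleep disorders have no effect, the crude risk ratio is

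(a·r + 1 − a) / (b·r + 1 − b).

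Worked case, a = 0.70, b = 0.50, r = 2: (1.40 + 0.30)/(1.00 + 0.50) = 1.70/1.50 = 1.13.

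The rejection columns give the simulated two-sided 5% rejection rate of the crude test at 200 vs 100 with 18% in the group without sleep disorders; the nominal rate is 5%.

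| Low activity, with vs without | Crude RR, r = 1.5 | r = 2 | r = 3 | Rejection, r = 1.5 | r = 2 | r = 3 |
|---|---|---|---|---|---|---|
| 50% vs 50% | 1.00 | 1.00 | 1.00 | 5% | 5% | 5% |
| 55% vs 45% | 1.04 | 1.07 | 1.11 | 5% | 6% | 7% |
| 60% vs 50% | 1.04 | 1.07 | 1.10 | 5% | 6% | 6% |
| 70% vs 50% | 1.08 | 1.13 | 1.20 | 6% | 7% | 11% |
| 60% vs 40% | 1.08 | 1.14 | 1.22 | 6% | 8% | 12% |
| 70% vs 40% | 1.13 | 1.21 | 1.33 | 7% | 12% | 21% |

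**Bias from SPPB group (rates from the plan, split assumed).** Suppose 55% of the 200 and 40% of the 100 are frail: 110 + 40 = 150, which respects the plan's 1:1 total. With no sleep effect the crude ratio is (0.55 × 27 + 0.45 × 9)/(0.40 × 27 + 0.60 × 9) = 18.9/16.2 = 1.17. So PASE is not the only factor that the primary estimate needs.

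**Can the data carry adjustment?** Expected events on the plan's inputs: 200 × 0.279 + 100 × 0.18 = 55.8 + 18 = 73.8. A model with sleep disorder, SPPB group, PASE, age and sex has 5 terms, so about 73.8/5 ≈ 15 events per term. Stratifying by PASE tertile within SPPB group is different. Healthy active participants without sleep disorders number about 50, with 50 × 0.09 = 4.5 expected events, or 1.5 per tertile. That is too sparse.

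**The case against.** **Adjustment is planned.** Multivariable logistic and ordinal models are named, and the Discussion promises covariate adjustment. A covariate list is commonly left to the analysis plan, so a reader may not conclude that PASE is used nowhere. This stands. It does not rescue the primary comparison, because the article itself ranks the adjusted model as interpretative.

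**The stratification has no stated purpose.** In a cohort, "stratified" may mean no more than classified, and no rule requires analysis to follow the strata as it would after stratified randomisation. This stands too. The point rests on confounding, not on such a rule, and the article does not say that PASE was chosen to control it.

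**Low activity may be a consequence of poor sleep.** The Background also says that worse sleep with ageing lowers activity, and PASE and PSQI belong to the same assessment. Adjusting for PASE could remove part of the effect of interest. This is a fair objection about the estimand, and it is why a version without PASE belongs beside the adjusted one.

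**Stronger readings that the documents do not support.** A reader might infer that activity differences will be reported as a sleep effect. The article documents neither an imbalance nor an activity–outcome association, so the bias is possible, not certain. A reader might also set a crude ratio of 1.13 against the 1.11 in Sample size and conclude that confounding alone meets the plan's criterion. But 1.11 is set for the lower confidence limit. At 18% vs 20.4%, a ratio of 1.13 has an expected 95% interval of about 0.69 to 1.87, and in simulation the lower limit exceeds 1.11 in about 2% of studies.

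**Conclusion.** The point holds in a limited form. For its primary endpoint the article fixes a crude test in a non-randomised cohort. The PASE stratification, and the adjustment that the Discussion relies on, therefore do not reach the primary result. This is a stated choice, not an omitted detail.

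The possible size runs from nothing to material. With low activity in 60% to 70% vs 50% and a 1.5- to 3-fold risk, a null effect appears as 1.04 to 1.20. At 55% vs 45% the false rejection rate barely moves from 5%; at 70% vs 40% it can reach about 21%. Every activity input is an assumption. If activity, SPPB group, age and sex turn out balanced across the sleep groups, the crude and adjusted estimates should be close. The case for change is bias; no gain in power is claimed.

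**What to change.** In Statistical methods, name as primary an adjusted risk ratio for sleep disorders with its 95% confidence interval, for example from modified Poisson regression with robust variance. Include SPPB group, baseline PASE as a continuous score, age and sex. Report as supportive (a) the crude two-proportion result and (b) the same model without PASE, and say that (b) is there because low activity may partly follow from poor sleep. State in one sentence what the PASE stratification at entry is for.

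The continuous score avoids the sparse cells that tertiles within SPPB group would create and needs no cut-points.

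The cost is a few sentences and a few lines of code. PASE, SPPB, age and sex are already collected. The change should be made before outcome data are examined. The remaining downside is a possibly conservative estimate if activity lies on the path from sleep to decline; the version without PASE lets readers see that.
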